### Data collection

Patient records and standardised forms will be used to collect baseline characteristics and outcome data. Outcome data is documented electronically as scheduled in the DMP.

Baseline characteristics include age, gender, first-language (usually spoken at home), educational status, body mass index (BMI), smoking status, blood pressure, LDL-cholesterol level, total cholesterol level, HbA1c level, current medication, and previous participation in diabetes and hypertension patient education programmes. Individual baseline risks of myocardial infarction are calculated by using a risk assessment tool. The tool uses age, smoking status, and clinical parameters and is derived from the Framingham function calibrated [61] to the average heart attack risk in the German population.

The treatment goals set by the individual patient in the ISDM group will be assessed after the teaching session and after the consultation by extracting them from the documentation sheet. Treatment goals of the control group will be assessed at a practice visit by using a standardised documentation form.

Telephone interviews will be conducted to assess the adherence to the current drug prescriptions. A standardised interview guide will be developed including questions such as *“Patients with diabetes often need to take several pills. I am interested in your current use of pills. Could you tell me, which medication boxes do you use? Which substances are labelled on the boxes?”*, and “*Have you ever missed any pills in the past seven days?”* [62]*.* Patients are classified as non-adherent if their answers are inconsistent with the prescriptions. Patients without antihypertensive prescription will be asked about statin medication. Patients with neither antihypertensive nor statin prescription will not be included in data analysis for the primary endpoint. In order to avoid socially desirable answers, the interviews will be conducted by a study assistant of the study organising centre, independent from the practices and blinded towards the allocation. Interviews will be audio-taped. In ambiguous cases, the tape will be analysed by a project member who is also blinded toward patients’ allocation. Inter-rater consensus will be achieved by discussion. Cholesterol levels at baseline and follow-up will be used to validate data on adherence to statin choice.

Informed choice [58] will be assessed, by grouping the patients into one of eight classifications according to their knowledge (adequate if score above the median), treatment goal (e.g. taking statin or not), and adherence (to statin choice). Participants will be assigned as having made an informed choice e.g. on taking statins if they have adequate knowledge, set the goal to take a statin and are adherent to this decision at six months follow-up. An informed choice against e.g. taking statins occurs if a patient has adequate knowledge, set the goal to not take a statin and is adherent to this decision at six months follow-up. We consider patients who had inadequate knowledge or whose treatment goal is not consistent with patient’s behaviour at six months follow-up, to have made an uninformed choice.

Achievement of treatment goals regarding blood pressure and HbA1c levels will be assessed during the doctor’s appointments at follow-up. Smoking status will be assessed during the telephone interview at follow-up by using a standardised interview question: “*On how many of the past 30 days did you smoke a cigarette?*” If patients have smoked any cigarettes in the past month, they will be classified as smokers. Current blood pressure values and HbA1c levels will be extracted from patient records.

Knowledge and understanding will be assessed directly after the teaching session. A standardised questionnaire consisting of 11 questions will be used to assess both comprehension of risk information and realistic expectations. Item analysis was performed using data from 143 patients, who participated in the ongoing pilot RCT [35]. Values of item difficulty were on average 37 (Range: 6 – 58), indicating moderate to difficult item difficulties. Corrected item-total correlations regarding total knowledge test were on average 0.57 (Range: 0.35 – 0.73), which were acceptable values, too. Initially, the test consisted of 12 items, but one item was deleted due to weak item total correlation (0.29). Internal consistency was calculated for the total knowledge test (Cronbach’s alpha = 0.87) and for the subdomain of realistic expectations (Cronbach’s alpha = 0.86). In sum, these results indicate good item parameters.

Prescribed medication will be extracted from patient records.

At follow-up, patients will be asked to indicate which information format they believe they have received to estimate the success of blinding (Table 2).

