## Methods

### Design

A parallel group, patient- and assessor-blinded, cluster randomised, controlled trial with six months follow-up will be conducted. Alongside the trial, qualitative methods will be used to achieve in-depth understanding of implementation processes.

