### Randomisation and blinding

Randomisation of practices will be performed after patient recruitment and retrieval of baseline data. To ensure close balance of entities in each group, randomisation will be performed in blocks of 4. The randomisation sequence will be generated by the Centre for Clinical Studies at the University Hospital Jena. Blinding of practices that deliver the intervention programme is not feasible. However, they will be asked to keep the allocation blinded as far as possible, i.e. to not reveal study details to the patients. Patients will be informed that the objective of the study is to compare two different approaches to better acknowledge patients’ preferences and values in decision making on preventive measures and that they have an equal chance of receiving the intervention or the control programme. Allocation concealment will be ensured for database entry and statistical analyses.

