#### Intervention group (ISDM programme)

The intervention programme (Table 1) comprises (1) an evidence-based patient DA [33] on the prevention of myocardial infarction, (2) a structured teaching module [32] provided by MAs, (3) a sheet to document the individual treatment goals, (4) a six hours provider training, and (5) an organisational study meeting with the personnel in the participating practice.

The DA includes evidence-based patient information on heart attack risk, risk factors, and different preventive options in an understandable manner [33]. In the development process, systematic literature search was performed for all recommended preventive options [33]. Information on the efficacy of preventive treatment has only been extracted from rigid RCT or high quality systematic reviews.

The DA guides users to estimate their individual risk of having a myocardial infarction in the next ten years and how it can be reduced by statin treatment. It provides information about the probable effects of more or less intensified glucose control and blood pressure control on the combined diabetes-related endpoint as used in the UKPDS [5,52].

The DA visualises text-based risk information by using combinations of 100-stick figure pictograms and bar graphs. An appendix provides additional information, e.g. reliability of individual risk prognosis. Important technical and medical terms are explained in a glossary.

The patient teaching module is curriculum-led and focuses on the EBPI provided in the DA. A teaching session targets groups of 4 to 6 patients and takes about 90 minutes. Two weeks before a session, the patients are asked to read and work through the DA [33]. During a session, the MA guides the patients through the decision making process. This encompasses assessing each patient’s individual heart attack risk, providing outcome probabilities of the available preventive treatment options, and supporting patients to set individual goals regarding smoking cessation, glucose control, blood pressure control, and statin treatment. Each patient notes individual preferences on treatment goals and the prioritised goal on a documentation sheet. Based on this, the patient and the GP deliberate and agree on treatment goals (Figure 1). This agreement is fixed on the documentation sheet for the patient to be taken home and documented in the patient record. The sheet can also supplement the patients’ diabetes management diary.

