**Table 2 Tab2:** **Data collection**

**Outcomes**	**Measures**	**Follow-up**
Adherence to antihypertensive or statin therapy	Prescription of antihypertensive drugs and statins (patient record)	T3
	Intake of antihypertensive medication or statins (structured telephone interview)	T3
Informed choice	Knowledge	T1
	Treatment goals: Statin choice, levels of blood pressure and HbA1c, and smoking	T1
	Achievement of goals regarding statins, blood pressure, HbA1c, and smoking	T3
Achievement of goals	Treatment goals: Statin choice, levels of blood pressure and HbA1c, and smoking as well as patient’s prioritised treatment goal (patient record)	T2
	Statin intake (structured telephone interview)	T3
	Blood pressure (standardised measure)	T3
	HbA1c level (laboratory value)	T3
	Smoking cessation (structured telephone interview)	T3
Prioritisation	Prioritised treatment goal: Statin choice, blood pressure, HbA1c or smoking cessation	T1, T2
Realistic expectations	Questionnaire developed based on the contents of the DA and the teaching module	T1
Knowledge	Questionnaire developed on the basis of Bloom’s taxonomy [65] and evidence-based information on heart attack prevention in type 2 diabetes [33]	T1

T1 = at the end of the teaching session; T2 = during physician consultation; T3 = at 6 months follow-up.

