## Discussion

In this cRCT, a novel SDM intervention will be compared with usual care in the setting of primary diabetes care.

The study has several strengths. The intervention is intended to promote the implementation of current guideline recommendations into practice, by systematically guiding patients together with their healthcare providers to deliberate on options and to set individual treatment goals in terms of SDM [1,8,20]. Patient teaching module and provider training are brief in their duration, which simplifies implementation into practice. Preliminary studies [32,33,35] have indicated good acceptance and feasibility.

The study has limitations. Firstly, it is impossible to keep the practices blind. At a kick-off symposium MAs and physicians have received information on the innovative ISDM approach to motivate them for participation in the study. Secondly, cluster designs in particular are susceptible for selection bias. This problem will be addressed by recruiting patients before randomisation. Thirdly, since it is not feasible to reliably assess SDM in the context of this study, we decided to use adherence to prescribed medication as an indirect measure. Similar to SDM, adherence is a behaviour influenced by subjective norms such as perceived attitudes of other individuals. Self-report can be biased by socially desired answers and pill count as a more objective measure is not feasible within this study. In order to avoid interfering with the intervention we will not assess self-reported adherence at baseline. Rather, medication prescriptions will be used as a surrogate to evaluate comparability of groups at baseline.

Fourthly, in order to reduce complexity we focused on the most relevant cardiovascular complication in type 2 diabetes, i.e. myocardial infarction. However, prevention requires a holistic approach. Issues such as stroke or microvascular complications are already addressed in the standard treatment and teaching programmes within the DMP, without however including numerical and comparative risk information. In order to communicate benefits and harms of blood glucose and blood pressure control we used UKPDS data [5,52] on the combined endpoint *any diabetes-related endpoint* which also includes other cardiovascular outcomes.

At the end of this study, information on the effectiveness of the ISDM programme and on processes that interfere with or promote a successful implementation into primary care practices will be available.

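### The trial is labelled assessor-blinded without limit, but follow-up blood pressure is assessed in unblinded practices, and the text does not tie it to the standardised measure in Table 2

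*Protocol article*

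**What the plan says.** On blinding, the Design section states: "A parallel group, patient- and assessor-blinded, cluster randomised, controlled trial with six months follow-up will be conducted". It sets no limit by outcome. The Randomisation and blinding section then says: "Blinding of practices that deliver the intervention programme is not feasible". The Discussion repeats this as its first limitation: "Firstly, it is impossible to keep the practices blind". Two safeguards are described. One concerns data handling: "Allocation concealment will be ensured for database entry and statistical analyses". The other concerns the telephone interviewer, who is "independent from the practices and blinded towards the allocation"; a project member who resolves unclear recordings is also blinded (Data collection).

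On blood pressure, the Data collection section places the assessment of goal achievement at the follow-up appointment with the doctor, and adds: "Current blood pressure values and HbA1c levels will be extracted from patient records". Table 2 lists the same T3 item as "Blood pressure (standardised measure".

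On targets, the intervention (ISDM) section says of the goals agreed by patient and GP: "This agreement is fixed on the documentation sheet for the patient to be taken home and documented in the patient record". Control patients are also asked to set goals (Control group), and these are recorded on a standardised form at a practice visit (Data collection).

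**The concern.** A reading taken by someone who knows the allocation can be rounded, repeated or selected, and blinding of assessors is meant to rule that out. For blood pressure, the people in a position to do so are practice staff. Masking the database and the analysis comes too late, because the value is already fixed in the record.

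Blood pressure enters three between-arm comparisons in the Secondary outcomes section: the difference between planned and achieved values, the change from baseline (T0) to T3, and informed choice on blood pressure, for which Table 2 lists goal achievement at T3 as a component. The Objectives also ask whether ISDM patients reach their blood pressure goals with fewer prescriptions, and the Outcomes section reads prescription changes in the light of goal achievement. A bias in the readings would carry over into that interpretation. If the article's readers accept the unlimited label, they will give these results the credibility of a blinded assessment.

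**Working it through.** **Who assesses what at T3**

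- Adherence, meaning reported intake of antihypertensives or statins: telephone interview from the study centre, blinded. Unclear cases go to a blinded tape reviewer.
- Smoking status: the same follow-up interview.
- HbA1c: a laboratory value (Table 2), retrieved from the record. The practice has little influence on the result.
- Blood pressure: assessed at the doctor's appointment and retrieved from the practice's record. The practice knows its allocation, and no blinded reader is described.

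The label in the Design section therefore holds for the interview outcomes and fails for blood pressure.

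**Are Table 2 and the text compatible?** Table 2 describes how the reading is taken; the text describes where the study retrieves it. Both can be true if a standardised reading is taken at the visit and filed. The text does not say so, and the Data collection section also says outcome data are documented on the disease management programme's schedule. A practice could comply with the text by supplying whatever value stands in the record. The two places are unreconciled.

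**Can the bias differ between arms?** Shared element: patients in both arms set goals, and Table 2 names the patient record as a source of goals without separating the arms. Unequal elements: only ISDM practices receive the six-hour training, and only they hold the GP consultation built on the goal sheet (Table 1 marks both as not applicable for control). The ISDM goal is filed in the same record from which the T3 value is later taken. Each practice also knows which programme it delivers.

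**Size (illustration only).** The documents give no blood pressure SD, no intracluster correlation for blood pressure and no estimate of reading bias.

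From the Sample size section: cluster size 13 and ICC 0.03, so the design effect is 1 + (13 − 1) × 0.03 = 1.36, as stated; 90 × 1.36 = 122.4, against 122 per arm stated. That ICC was chosen with the adherence endpoint in mind; using it for blood pressure is my assumption.

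Standard error of the arm difference = SD × √(2/122) × √1.36. With an assumed SD of 15 mmHg: 15 × 0.1280 × 1.1662 = 2.24 mmHg. A differential bias of 3 mmHg is 3/2.24 = 1.34 standard errors; 5 mmHg is 5/2.24 = 2.23.

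False-positive rate with no true difference and bias b: 1 − Φ(1.96 − b/SE) + Φ(−1.96 − b/SE).

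| Differential bias | SD 12 | SD 15 | SD 18 |
|---|---|---|---|
| 0 mmHg | 5% | 5% | 5% |
| 2 mmHg | 20% | 15% | 12% |
| 3 mmHg | 39% | 27% | 20% |
| 5 mmHg | 80% | 61% | 46% |

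The planned test is an ordinary unpaired t-test, without the design effect. Its standard error at SD 15 is 15 × √(2/122) = 1.92 mmHg, so a smaller shift would reach nominal significance: 1.96 × 1.92 = 3.8 mmHg, against 1.96 × 2.24 = 4.4 mmHg.

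**The case against.** The strongest reply has four parts.

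First, a reader might infer that Table 2 and the text contradict each other and that the outcome is merely a routine reading. The documents do not support that. HbA1c shows the same pattern: Table 2 calls it a laboratory value, and the same sentence of the text takes it from the record. The Data collection section also names standardised forms as a source. Device, number of readings and operator instructions may well stand in the full protocol, so their absence from the article is no fault. This part stands: the passages need reconciling, but they are not incompatible.

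Second, control patients also set recorded goals, so rounding toward a target may occur in both arms and partly cancel. The goal is agreed at the consultation (T2), not just before the T3 reading. This also stands. It reduces the expected differential bias without removing it, because training, the goal-sheet consultation and knowledge of the allocation remain unequal.

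Third, the protocol admits that practices are unblinded and names its blinded interviewer, so a careful reader can work out which outcomes are protected. This stands only in part: the Discussion does not apply the limitation to blood pressure, and the label in the Design section has no qualifier.

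Fourth, the numbers rest on assumed inputs. A bias of 5 mmHg would have to be a mean shift over all patients. The Outcomes section compares group differences in blood pressure rather than classing each patient against a cut-off, so nudging borderline readings moves the mean less than it would move a responder rate. This stands, and the table above is therefore no estimate.

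**Conclusion.** The point holds in a limited form. The unqualified assessor-blinded label is wrong for blood pressure, where the described assessors are practice staff who know their allocation. Planned-minus-achieved blood pressure, change from T0 to T3 and informed choice on blood pressure are open to observer bias that may be partly shared but can differ between arms. The text should also say whether the extracted value is the standardised measure in Table 2.

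The size cannot be derived from the documents. The illustration shows only that, for SDs of 12 to 18 mmHg and the plan's own design effect, a differential shift of 2 to 3 mmHg would already distort the error rate noticeably.

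A reader might infer that the programme's blood pressure results will be biased in its favour, or that the primary result is compromised. Neither follows. The documents show an exposure to bias, not its presence or amount. The intake component of the primary endpoint comes from a blinded interviewer independent of the practices, and HbA1c is a laboratory value; both are largely unaffected. This is a matter for secondary and additional outcomes: worth correcting, but no threat to the main comparison.

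**What to change.** 1. In the Design section, restrict the assessor-blinded claim to the outcomes collected by telephone interview. In the Data collection section and the Discussion, state that the blood pressure outcomes are assessed by unblinded practice staff, and report them as such.
2. In the Data collection section, state that the T3 blood pressure is the standardised measure of Table 2, taken in the same way in both arms.
3. Have all readings from that measurement entered on the study form, and compute the mean centrally rather than taking one value from the record. The reader remains unblinded, but there is less room to select or repeat readings.

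The cost is protocol wording, a short form and a few minutes per patient at an existing visit. The blinding claim becomes narrower. T0 values may have been measured differently from T3 values, which affects the interpretation of the change within each arm. Because baseline data are collected before randomisation, any such difference in method should be the same in both arms and should not by itself bias the comparison.

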**Table 2 Tab2:** **Data collection**

**Outcomes**	**Measures**	**Follow-up**
Adherence to antihypertensive or statin therapy	Prescription of antihypertensive drugs and statins (patient record)	T3
	Intake of antihypertensive medication or statins (structured telephone interview)	T3
Informed choice	Knowledge	T1
	Treatment goals: Statin choice, levels of blood pressure and HbA1c, and smoking	T1
	Achievement of goals regarding statins, blood pressure, HbA1c, and smoking	T3
Achievement of goals	Treatment goals: Statin choice, levels of blood pressure and HbA1c, and smoking as well as patient’s prioritised treatment goal (patient record)	T2
	Statin intake (structured telephone interview)	T3
	Blood pressure (standardised measure)	T3
	HbA1c level (laboratory value)	T3
	Smoking cessation (structured telephone interview)	T3
Prioritisation	Prioritised treatment goal: Statin choice, blood pressure, HbA1c or smoking cessation	T1, T2
Realistic expectations	Questionnaire developed based on the contents of the DA and the teaching module	T1
Knowledge	Questionnaire developed on the basis of Bloom’s taxonomy [65] and evidence-based information on heart attack prevention in type 2 diabetes [33]	T1

T1 = at the end of the teaching session; T2 = during physician consultation; T3 = at 6 months follow-up.

### Data synthesis

All statistical analyses are carried out according to the intention-to-treat principle. Missing data will be imputed using the method of multiple imputation if feasible. All analyses will be computed using IBM SPSS Statistics 22.0 for Windows.

Baseline characteristics are described using means of standard deviation (± SD) or frequencies, as appropriate according to the level of measurement.

#### Primary outcome

Fisher’s exact test will be used to compare the groups regarding the adherence to antihypertensive or statin therapy.

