#### Secondary outcomes

Fisher’s exact test will be used to compare the groups regarding 1) the informed choice regarding statin treatment, smoking, blood pressure and HbA1c; 2) rates of individual goal achievement (yes/no): statin choice, smoking status; and 3) rates of changed treatment goals.

Unpaired t-tests will be used to compare the study groups regarding 1) the average difference between planned and achieved values of blood pressure; 2) the average difference between planned and achieved level of HbA1c; and 3) the level of realistic expectations and knowledge.

Mann–Whitney *U*-test will be used to compare the medication prescription from T0 to T2, T3 (increase/unchanged/decrease).

Unpaired t-tests will be used to compare the study groups regarding 1) the change of clinical parameters (HbA1c, blood pressure, cholesterol) from T0 to T3 and 2) the mean difference between perceived risk and assessed risk between groups.

Difference in the chosen prioritised treatment goals between groups will be compared by using chi-square test.

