### Sample size

We hypothesise patients in the ISDM group to reach higher adherence to prescriptions of antihypertensive and statin medication.

Based on current DMP-data [39] and the preliminary results of the pilot RCT [35], we assume that approx. 60% of patients in the control group will adhere to the choice. We estimate that more than 80% of patients in the intervention group will adhere.

We calculate the sample size providing 80% power to detect an absolute difference of 20% between the intervention and the control group, using Fisher’s exact test at the 5% level of significance. Thus, in a non-cluster RCT data on about 90 patients per group (180 participants) would need to be included in data analysis.

Since observations on individuals in the same cluster tend to be non-independent, the effective sample size is less than the total number of individual participants. The reduction in effective sample size depends on the average cluster size (m) and the degree of correlation within clusters (intracluster correlation coefficient, ICC). To retain power, the sample size should be multiplied by the so-called design effect (DE = 1 + (m - 1) × ICC) [36]. However, we did not identify data, allowing an estimation of a probable ICC for the primary endpoint used in our study. Krones et al. [28] reported an ICC of 0.06 for an endpoint relating to patient participation. Branda et al. [63] published an ICC of 0 or nearly 0 for knowledge, decisional comfort, and medication adherence. Thus estimating an ICC of 0.03 and a mean cluster size of 13 participants, we calculate with a design-effect of DE = 1.36. Hence, data on 122 patients per study arm (total 244 participants) need to be included in data analysis. Estimating a drop-out rate of about 20%, 306 participants will be recruited for randomisation, distributed across 24 clusters (practices). This power calculation was conducted by [name] Biostatistician (Jena, Germany).

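### The primary test and all secondary tests treat patients as independent although practices are randomised, so the 5% level is exceeded at the plan's own ICC

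*Protocol article*

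**What the plan says.** All references are to the protocol article.

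- **Unit of randomisation** (Randomisation and blinding): "Randomisation of practices will be performed after patient recruitment and retrieval of baseline data".
- **Primary analysis** (Primary outcome): "Fisher’s exact test will be used to compare the groups regarding the adherence to antihypertensive or statin therapy". This is the whole of that subsection.
- **Secondary analyses** (Secondary outcomes): for binary outcomes, "Fisher’s exact test will be used to compare the groups regarding 1) the informed choice regarding statin treatment, smoking, blood pressure and HbA1c"; for continuous outcomes, "Unpaired t-tests will be used to compare the study groups regarding 1) the average difference between planned and achieved values of blood pressure". Changes in prescriptions get a Mann–Whitney test and prioritised goals a chi-square test.
- **Dependence** (Sample size): "observations on individuals in the same cluster tend to be non-independent". The section assumes an ICC of 0.03 and a mean of 13 patients per practice, and applies the resulting design effect of 1.36 to the patient numbers. It also cites an ICC of 0.06 for a patient participation endpoint, and values at or near 0 for several endpoints including medication adherence. It says that no ICC data were found for this trial's primary endpoint.

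The Data synthesis section contains no random effect, GEE, practice-level summary or variance correction.

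**The concern.** Each named test takes its null variance from independent patients. When practices are allocated and patients within a practice resemble one another, the difference between arms varies more under the null than these tests allow. Raising the number of patients by a design effect restores power. It leaves the test's reference distribution uncorrected. For a fixed ICC and number of practices, more patients per practice makes an unadjusted test more liberal.

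At stake is the main inference: a primary result declared significant at 5% would carry a higher false-positive risk than stated, under the correlation that the plan itself assumes. The same applies to the secondary comparisons.

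**Working it through.** **1. Inputs, all from the Sample size section unless noted.** Adherence 60% against 80%; 5% level (sidedness is not stated, but two-sided reproduces the figure); 80% power; ICC 0.03; m = 13; 122 analysed per arm; 20% drop-out; 306 recruited; 24 practices. Equal allocation in blocks of 4 (Randomisation and blinding) gives 12 practices per arm.

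**2. The plan's own figure reproduces.**
- Exact power of the two-sided Fisher test is 79.6% with 89 per group and 80.2% with 90, so 90 per group is right.
- DE = 1 + (13 − 1) × 0.03 = 1.36; 90 × 1.36 = 122.4, stated as 122 per arm.
- 122 / 0.8 = 152.5, rounded up to 153 per arm, or 306 in total.

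The sample size is sound as stated. The problem lies in the analysis.

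**3. Analytic approximation.** An unadjusted z-test has true size 2(1 − Φ(1.96/√DE)). The analysed cluster size is 244/24 = 10.17.
- ICC 0.03: DE = 1 + 9.17 × 0.03 = 1.275, size 8.3%.
- ICC 0.06: DE = 1 + 9.17 × 0.06 = 1.55, size 11.5%.

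Fisher's test is conservative, so this formula overstates its size and simulation is needed.

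**4. Simulation for the primary test.** Beta-binomial outcomes, 12 practices per arm, near-equal practice sizes, 100,000 runs. The null was run at 60% and at 70% adherence; power is for 60% against 80%.

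| ICC | Fisher size, 122 per arm | Fisher size, 13 per practice (156 per arm) | Practice-level t-test (22 df) size, 122 per arm | Its power, 122 per arm |
|---|---|---|---|---|
| 0 | 3.6–3.7% | 3.7–3.9% | 5.0% | 91% |
| 0.01 | 4.6% | 5.0–5.1% | 4.9–5.1% | 89% |
| 0.03 | 6.4–6.5% | 7.6% | 5.0% | 83% |
| 0.06 | 9.4–9.6% | about 11.3% | 5.1% | 76% |

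Separate simulations with 122 per arm gave 3.5–3.8%, 4.6–4.7%, 6.3–6.6% and 9.2–9.6% for the Fisher test at the four ICC values.

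**5. Unequal practice sizes.** The article gives no distribution of practice sizes. With an assumed coefficient of variation of about 0.45 and 122 per arm, Fisher's size was 7.0–7.3% at ICC 0.03 and 10.5–10.7% at 0.06. The power of an unweighted practice-level t-test fell to 77% at ICC 0.03.

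**6. Secondary t-tests.** Normal outcomes with a practice effect, 12 practices of 10 patients per arm: size 4.9% at ICC 0, 8.2% at 0.03 and 11.4% at 0.06. These figures assume that the same ICC values apply to the secondary outcomes. The Mann–Whitney test was not simulated; it rests on the same independence assumption.

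**The case against.** **The cited ICC for medication adherence is at or near zero.** It is the cited endpoint closest to the primary outcome, and the 0.06 belongs to a different kind of endpoint. This stands as a limit on the size of the problem: at ICC 0.01 Fisher's own conservatism keeps the error at about 4.6–5.1%. It does not rescue the plan, which says that no ICC for its endpoint was found and chose 0.03 for itself. It cannot assume 0.03 for the sample size and in effect 0 for the test.

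**A condensed article may leave cluster adjustment to a fuller plan.** It may leave detail, but this article is not silent. It names the primary test in the analysis section and again as the basis of the power calculation, and that test contradicts the dependence that it describes.

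**Stronger readings that the document does not support:**
- A reader might infer that the trial's confidence intervals will be too narrow. The analysis section plans no confidence intervals. The remark would apply only to intervals later computed on the same patient-level basis.
- A reader might infer that Fisher's test and the missing-data plan cannot coexist, or that imputation will ignore practice. The text says only "Missing data will be imputed using the method of multiple imputation if feasible". That is not a firm commitment for the primary outcome, nothing says that practice would be left out, and the imputation model and pooling rule are details an article may leave to the full plan.
- A reader might infer that the 5% level fails whatever the ICC, or that the planned number suffices for a valid analysis in every case. Both depend on the ICC, as the table shows.

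**Conclusion.** The point holds. The article fixes tests that assume independent patients in a trial that randomises practices and states that patients within them are correlated. This is a wrongly specified method, not an omission.

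For the primary test with 122 analysed per arm, the excess over 5% is moderate at the plan's ICC of 0.03 (true size about 6.3–6.5%) and large at 0.06 (about 9.5%). With 13 analysed per practice the figures are about 7.6% and 11%. The unpaired t-tests lack Fisher's conservatism and reach about 8% and 11%. At an ICC of about 0.01 or below, the Fisher test roughly holds its level. The primary-test figures assume 12 practices per arm, near-equal practice sizes and beta-binomial variation; unequal sizes make the inflation worse.

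**What to change.** Replace the primary test with one cluster-adjusted analysis, named in advance. Suitable choices are:
- a t-test of practice-level adherence proportions on 22 degrees of freedom, or
- a logistic mixed model with a random practice effect, or GEE, with a small-sample correction for 24 practices.

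Use corresponding cluster-adjusted analyses for the binary, continuous, ordinal and categorical secondary outcomes. Settle the estimator and any weighting for unequal practice sizes now, because they affect power.

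The change is to analysis wording only and needs no further data. At the planned size, a practice-level t-test has about 83% power at ICC 0.03 with near-equal practice sizes, so the design supports a valid analysis under its own assumptions. That margin is not assured. Power is about 76% at ICC 0.06, lower if practice sizes are unequal, and lower again if the exclusion of patients with neither an antihypertensive nor a statin prescription (Data collection) takes the analysed number below 244. The sponsor should state this when making the change.
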